#### Ryff’s Scale of Psychological Well-Being and Quality of Life

The Ryff’s Scale of Psychological Well-being (SPWB) and World Health Organization Quality of Life Assessment (WHOQL-BREF) will be used in this study to assess the psychological well-being and quality of life among adolescents with ACEs. These instruments have been validated among the Malaysian population with acceptable discriminant validity, construct validity, and test-retest reliability greater than the threshold value of 0.5 [52-54].

#### Personal Resources Questionnaire 2000

The personal resources and workability of the participants will be assessed using the Work Ability-Personal Radar (WA-PR) instrument, which has been previously translated into Malay and validated by Hamdan et al [55]. The instrument has adequate psychometric properties and has been validated with acceptable discriminant validity, construct validity, and test-retest reliability greater than the threshold value of 0.5, making it suitable to be used in investigating personal resources and workability levels in the Malaysian population [55].

#### The Perceived Stress Scale-10

The Perceived Stress Scale-10 (PSS-10) is generally used in assessing stress perception. The Malay version of the PSS-10 has been validated among diverse populations in Malaysia, with the latest being nurses from government hospitals [39]. The instrument revealed acceptable internal consistency with a Cronbach α value of 0.63 and intraclass correlation coefficient of 0.81 (95% CI 0.62-0.91) following a 7-day test-retest reliability analysis. Furthermore, previous studies found significant correlations between the stress component of Depression Anxiety and Stress Scale 21 and the total score and negative component of the PSS-10 (r=0.56-0.61). Therefore, the PSS-10 is considered valid and suitable for investigating stress perception among Malaysian youths, including adolescents [56].

#### Saliva Cortisol and Blood Pressure Assessment

Each participant will be instructed to provide approximately 2 mL of whole saliva by passive drool, which will be then split into multiple 100 uL aliquots and frozen immediately. One aliquot of each of the 50 participants’ saliva will be transported overnight on dry ice to the institutional laboratory. Cortisol analysis will be performed using commercially available immunoassay according to the manufacturer’s guidelines (Salimetrics). Meanwhile, participants’ blood pressure will be measured objectively with a sphygmomanometer.

#### Time Points for the Primary Outcomes and Retention

Premeasurements will be conducted at baseline, whereas postmeasurements will be collected after the fifth session as shown in Figure 1. Participants will be given Ringgit Malaysia 50 after the third and fifth sessions of the intervention to ensure they do not drop out of the study. Another follow-up will be conducted 4 weeks after the Intervention.

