## Methods

### Study Design and Setting

This is a 2-armed, single-blinded, randomized controlled trial (RCT) that will be conducted among Malaysian youths with ACEs at the Department of Clinical and Health Psychology, National University of Malaysia. Briefly, the intervention group includes an evidence-based curriculum and components such as emotion regulation, active coping and goal setting, cognitive flexibility, mindfulness-based stress reduction, social support, self-exploration, resources and navigation, and finally, spirituality and religion. Participants in the control group will not receive any form of intervention. The main outcome of this study is resilience among youths with ACE while the secondary outcomes include coping, psychological well-being, quality of life, subjective stress, perceived stress, personal resources, and adult resilience. These variables will be evaluated at baseline and postintervention. Intention-to-treat analysis will also be performed. This clinical trial has been registered with the Australia New Zealand Clinical Trials Registry (trial Id: ACTRN12622000604707).

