**Assessments**										
	Brief Coping Orientation to Problem Experienced Scale - English and Malay version	✓				✓		✓		
	Ryff’s Scale of Psychological Well-being (SPWB) - English and Malay version	✓				✓		✓		
	Quality of Life –WHOQL-BREF - English and Malay Version	✓				✓		✓		
	Subjective stress – Perceived Stress scale - English & Malay version	✓				✓		✓		
	Personal Resources Questionnaire 2000 - English and Malay version	✓				✓		✓		
	Adult Resilience Measure-Revised - English and Malay version	✓				✓		✓		
	Biomarker - measure changes in salivary cortisol	✓				✓				
	Blood pressure (blood pressure measured with a sphygmomanometer	✓				✓				

Participants in the control group will receive no intervention, while those in the intervention group will receive five sessions of resilience-building intervention conducted by a trained facilitator. Hotlines, post session, and appropriate resources will be provided for those reporting distress after the intervention. Investigators will be blinded throughout the whole process of randomization and data collection as the whole process is handled by a research assistant (randomization), counsellor, and clinical psychologist (data collection). Under no circumstances will unbundling occur as a research assistant, counsellor, and clinical psychologist are briefed with the standard operating procedure to follow when an incident occurs. The flow diagram is presented in Figure 1.

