### Data Analysis

All data management and statistical analysis will be conducted using SPSS (version 26; IBM Corp). Data management will be performed by screening for missing data and checking for potential outliers. Descriptive statistics will be used to assess the data normality and to summarize the pre and postintervention scores for each group at different periods. Mean and SDs will be provided for normally distributed data, followed by mixed ANOVA with repeated measures to compare the pre and postintervention mean scores between and within the groups.

The assumptions of ANOVA include randomly collected and normally distributed data, sufficient sample size, homogeneity of variances, and absence of violation and outliers. Levene’s test will be applied to test the homogeneity of variance. Mixed ANOVA benefits RCT design as it allows testing for 2 groups across 2-time points. Mixed ANOVA analysis aims to handle response outcomes conducted on the same experimental unit at a different time or under different conditions [57]. The differential effects of the intervention components will be tested with interactions between the component and time. These analyses will model random slopes and intercepts for participants, explore the fixed effects of the condition, and test the repeated measures over time. This type of analysis is advantageous by accounting for missing values through the maximum likelihood estimation method [57]. Effect sizes will be computed based on Cohen *d*.

In addition, the intention-to-treat analysis will be applied to analyze the participants according to their assigned groups. This analysis includes all participants and ignores noncompliance, protocol deviation, and withdrawal. The intention-to-treat analysis is a complete trial strategy for the design, execution, and analysis of RCT, focusing on the consolidated standard of reporting trial guidelines. Thus, the number of participants in each assigned group will be analyzed by the intention-to-treat principle.

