As for missing data, drop-out in this study refers to participants who withdraw actively from the intervention post randomization. All cases of dropouts will be considered in the intent-to-treat samples since they have been randomized and included in the analysis. The extent and pattern of missing data will be assessed, and depending on the results, missing values will be replaced by using multiple imputations. The impact of the imputation of missing values will be further explored by conducting sensitivity analyses.

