#### Criteria for Discontinuing or Modifying Intervention

All the intervention modules were well understood by the participants enrolled in the pilot test; hence, no attempt has been made to review the intervention. Participants have the right to withdraw from the research at any given time if they do not feel comfortable continuing with the study. If the counselor or clinical psychologist reviews and discusses the harm of the participants continuing to participate in the research project, they will advise the participants to drop out of the study based on their professional judgment. A panel comprising counselors, and clinical psychologists will jointly review the case and make a consensus decision.

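### The only stated retention payment is tied to intervention sessions that controls do not have, which risks unequal loss between the arms

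*Protocol article*

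**What the plan says.** Under Time Points for the Primary Outcomes and Retention, the protocol article states: "Participants will be given Ringgit Malaysia 50 after the third and fifth sessions of the intervention to ensure they do not drop out". No other retention payment appears. The same paragraph says that "postmeasurements will be collected after the fifth session as shown in Figure 1" and that "Another follow-up will be conducted 4 weeks after the Intervention", with no payment attached to the follow-up visit.

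The text after Table 1 (Participant Recruitment and Randomization) says: "Participants in the control group will receive no intervention, while those in the intervention group will receive five sessions of resilience-building intervention". The Abstract and Study Design and Setting agree that controls get nothing.

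On the outcomes, Study Design and Setting says: "These variables will be evaluated at baseline and postintervention". Data Analysis describes the comparison this way: "Mixed ANOVA benefits RCT design as it allows testing for 2 groups across 2-time points". In its missing-data paragraph, "drop-out in this study refers to participants who withdraw actively from the intervention post randomization". The section also plans intention-to-treat analysis, maximum likelihood, an assessment of the extent and pattern of missing data, multiple imputation if needed, and sensitivity analyses on the imputation. Sample Size allows for 50% drop-out as a single rate, not split by arm.

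**The concern.** The payment exists to prevent drop-out, yet the event that triggers it occurs in one arm only. It also rewards attending sessions rather than giving outcome data. If controls are not paid, the two arms have different reasons to stay, so both the rate of loss and the kind of person lost can differ between them.

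When leaving depends on the unobserved outcome, unequal loss biases the between-arm contrast. Intention-to-treat labelling does not cure that. Maximum likelihood and multiple imputation in their standard form assume data missing at random, and the planned sensitivity analyses are not described as covering other mechanisms. They could show such bias but not remove it.

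The drop-out definition adds to the problem. It refers to withdrawal from the intervention, which a control participant cannot do.

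**Working it through.** **The plan's own figure.** Sample Size gives N = 36 for f = 0.25, alpha 0.05 and power 0.80. The correlation and number of measurements are not stated. For the within-between interaction, lambda = f² x N x m / (1 - rho), with df (m - 1) and (N - 2)(m - 1). Taking m = 2 and rho = 0.5 (assumed):

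- N = 34: lambda = 0.0625 x 34 x 2 / 0.5 = 8.5, power 0.807.
- N = 36: lambda = 9.0, power 0.83.

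So 36 reproduces to within two participants. Enrolling 50 leaves 36 after a loss of 1 - 36/50 = 28%, which is the equal-loss case below.

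**Payment as worded, by arm.**

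| | Intervention | Control |
|---|---|---|
| Sessions | 5 | 0 |
| After session 3 | RM50 | none stated |
| After session 5 | RM50 | none stated |
| 4-week visit | none stated | none stated |

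It is unclear whether RM50 is paid once or twice. The table takes it as paid twice.

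**Bias under assumed retention.** The inputs are 25 per arm (Sample Size) and, as assumptions, no true effect, pre-post correlation 0.5, and logit P(leave) = a(arm) + ln(OR) x outcome in SD units. OR is 2 or 3, and a(arm) is set to give the chosen loss. The analysis is a baseline-adjusted, two-sided 5% test in completers, with 8,000 runs per scenario. Simulation error on a 5% rate is sqrt(0.05 x 0.95 / 8000) = 0.24 percentage points.

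| Retention, intervention v control | Bias (SD), OR 2 to 3 | False-positive rate |
|---|---|---|
| 90% v 70% | 0.09-0.13 | 5.6-7.7% |
| 90% v 50% | 0.19-0.26 | 8.8-13.1% |
| 72% v 72% | about 0 | about 5% |

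The sign depends on who leaves. If those doing well leave more often, the better-retained arm looks better; if those doing badly leave, it looks worse.

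**Cruder cross-check.** If leavers differ from stayers by 0.5 SD in both arms (assumed), the completer contrast shifts by 0.5 x the difference in loss. Loss of 10% v 28% gives 0.5 x 0.18 = 0.09 SD, and 10% v 50% gives 0.5 x 0.40 = 0.20 SD. This is the same order.

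**Relative to the planned effect.** Read as a simple group difference, f = 0.25 is d = 2f = 0.5, so 0.09-0.26 SD is roughly a fifth to a half of it. The interaction formula above with m = 2 corresponds to a difference in change of 4f = 1.0 SD, so the bias is then roughly a tenth to a quarter.

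**Data so far.** Results reports 28 enrolled, 14 per arm, with 2 withdrawals in the intervention arm and nothing said about controls. That is 2/14 (exact 95% CI 1.8% to 42.8%) against 0/14 if silence means none (0% to 23.2%), Fisher p = 0.48. It does not settle the direction.

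**The case against.** The strongest reply is that the payment sentence refers to participants without naming an arm. The same paragraph already uses the fifth session to time the post-measurements, which Table 1 does not restrict to one arm. Sessions are weekly, so the third and fifth sessions could mean weeks 3 and 5 for everyone, with details left to the full protocol or consent form. This stands as a possible reading: a reader might infer that controls are certainly unpaid, and the article does not say so. Even so, the stated trigger does not exist for half the sample and has to be corrected.

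Second, a reader might infer that unequal attrition is built into the main comparison. That turns a risk into a certainty. Five sessions of about two hours may drive loss in the intervention arm, and the only reported withdrawals are there.

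Third, a reader might count the unpaid 4-week visit as a bias in the main comparison. That comparison is described as baseline to postintervention, and a visit unpaid in both arms is not differential by itself. It is a retention weakness only.

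Fourth, it would be too strong to say that control losses go uncounted. Intention-to-treat covers all randomised participants, the pattern of missing data will be assessed, and a CONSORT flow diagram is provided. What stands is that the drop-out definition does not fit controls.

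Fifth, cash received at about the time of the post-measures might be thought to alter self-reported stress or quality of life. The documents give nothing from which to size this, so no weight is placed on it.

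Finally, all arm-specific retention rates and odds ratios are assumed. Equal payment cannot guarantee the same loss process when one arm attends sessions and the other does not.

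**Conclusion.** The concern holds as a risk created by the stated payment rule. Retention money is triggered by sessions that only one arm has and is not linked to giving outcome data, while the plan itself allows for heavy drop-out. On the natural reading the arms have unequal incentives to stay. Whether controls are in fact unpaid, and which arm would lose more, cannot be settled from the article.

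The illustrated bias, about 0.09 to 0.26 SD, requires both unequal loss and leaving that depends on the unobserved outcome (odds ratio 2-3 per SD). It comes from a baseline-adjusted completer analysis rather than the planned mixed ANOVA. At the milder retention gap, the false-positive rate rises only modestly. The change is worth making because it is specific and cheap and removes one avoidable source of imbalance.

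**What to change.** 1. In Time Points for the Primary Outcomes and Retention, replace the session-based payment. Every randomised participant, in both arms and whether or not sessions were attended, receives the same amount for completing the postintervention assessment and the same amount for completing the 4-week assessment.
2. In the missing-data paragraph of Data Analysis, define drop-out as loss from the study in either arm, and record withdrawal from the intervention separately.
3. Report completion of each assessment by arm.
4. For participants already enrolled, apply the new rule to assessments still due, and state what controls were paid up to then. Recruitment was expected to finish by 30 January 2025. If it has closed and no assessments are due, that statement and completion by arm are what remains to be done.

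**Cost.** If RM50 is paid twice now to the intervention arm only, the outlay is 25 x RM100 = RM2,500. RM25 + RM25 for all is 50 x RM50 = RM2,500, which is cost-neutral but halves the payment per intervention participant. RM50 + RM50 for all is 50 x RM100 = RM5,000, or RM2,500 more. If RM50 is the total now, the present outlay is 25 x RM50 = RM1,250, and RM25 + RM25 for all adds RM1,250. The change also needs a short ethics amendment, leaves two payment regimes in a sample of 50, and may slightly lower session attendance.

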### Data Analysis

All data management and statistical analysis will be conducted using SPSS (version 26; IBM Corp). Data management will be performed by screening for missing data and checking for potential outliers. Descriptive statistics will be used to assess the data normality and to summarize the pre and postintervention scores for each group at different periods. Mean and SDs will be provided for normally distributed data, followed by mixed ANOVA with repeated measures to compare the pre and postintervention mean scores between and within the groups.

The assumptions of ANOVA include randomly collected and normally distributed data, sufficient sample size, homogeneity of variances, and absence of violation and outliers. Levene’s test will be applied to test the homogeneity of variance. Mixed ANOVA benefits RCT design as it allows testing for 2 groups across 2-time points. Mixed ANOVA analysis aims to handle response outcomes conducted on the same experimental unit at a different time or under different conditions [57]. The differential effects of the intervention components will be tested with interactions between the component and time. These analyses will model random slopes and intercepts for participants, explore the fixed effects of the condition, and test the repeated measures over time. This type of analysis is advantageous by accounting for missing values through the maximum likelihood estimation method [57]. Effect sizes will be computed based on Cohen *d*.

In addition, the intention-to-treat analysis will be applied to analyze the participants according to their assigned groups. This analysis includes all participants and ignores noncompliance, protocol deviation, and withdrawal. The intention-to-treat analysis is a complete trial strategy for the design, execution, and analysis of RCT, focusing on the consolidated standard of reporting trial guidelines. Thus, the number of participants in each assigned group will be analyzed by the intention-to-treat principle.

As for missing data, drop-out in this study refers to participants who withdraw actively from the intervention post randomization. All cases of dropouts will be considered in the intent-to-treat samples since they have been randomized and included in the analysis. The extent and pattern of missing data will be assessed, and depending on the results, missing values will be replaced by using multiple imputations. The impact of the imputation of missing values will be further explored by conducting sensitivity analyses.

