**Methods:**

The is a 2-armed, single-blind, RCT, whereby 50 participants (25 in each group) with ACEs will be randomly assigned to intervention and control groups. The former will be exposed to a resilience-building program (R2), which entails a multisystemic approach to resilience and recognizes the importance of rugged qualities and access to resources among individuals affected with ACEs. The intervention will be delivered via internet-based by a facilitator and broadly divided into 5 sessions, focusing on self-exploration and social support, coping techniques and coping skills, resource finding, spirituality, and resilience building. Meanwhile, the control group participants will not receive any form of intervention. Saliva samples will also be collected from both groups and assessed for salivary cortisol levels. Outcome measures will be assessed during baseline and postintervention using validated instruments. Another follow-up measurement will be conducted 4 weeks later.

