#### Sample Size

Sample size calculation was performed using G*power 3.1 software (Heinrich-Heine-Universität Düsseldorf). By assuming a study power of 0.8, 95% CI (α=0.05), and a moderate effect size of 0.25 as recommended by Ferguson (2009), the *F*-test was selected alongside repeated measures ANOVA with in-between interaction, with 2 groups and the number of measurements. Thus, a total sample size of 36 was obtained, reflecting 18 participants per group. We considered a high drop-out rate of 50% as several individuals may be unwilling to participate given the adverse effects of ACEs and confidentiality in sharing experiences with the researchers. Therefore, the sample size was increased to 50, amounting to 25 participants per group.

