#### Intervention Protocol and Fidelity

The intervention will be conducted in Malay or English. It aims to encompass both languages and will be provided according to the participant’s native language. Therapists will be trained to follow the protocol and the manual. A recap will be conducted at the end of the session. Dynamic assessment will be used to track the learning progress. Participants will use journaling as a method to practice their skills. In addition, progress and practice will be discussed at the beginning of each session. As for intervention fidelity, journals and progress of group sessions will be collected from mental health professionals after each session to ensure they continue a similar structure for the intervention. The checklist will be prepared for the mental health professional.

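### The stated pre/post mixed ANOVA is less precise than a baseline-adjusted model, gives the 4-week questionnaires no place, and is described with features that a mixed ANOVA does not have

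*Protocol article*

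**What the plan says.** The Data Analysis section compares scores before and after the intervention by "mixed ANOVA with repeated measures to compare the pre and postintervention mean scores between and within the groups". It justifies this choice by the design of two groups and two time points, and it names no baseline covariate. The checks listed are those of an ANOVA, including Levene's test.

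Later in the same paragraph the analysis is said to include random slopes and intercepts for participants, and the protocol adds: "This type of analysis is advantageous by accounting for missing values through the maximum likelihood estimation method". On the analysis set, the section says of intention to treat: "This analysis includes all participants and ignores noncompliance, protocol deviation, and withdrawal". It keeps drop-outs in the sample, allows multiple imputation depending on the extent and pattern of missing data, and plans sensitivity analyses of the imputation.

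The schedule has three measurements, not two. The Abstract says: "Another follow-up measurement will be conducted 4 weeks later". The section on time points for the primary outcomes repeats this. Table 1 ticks all six questionnaires at enrolment, postintervention and the 4-week follow-up, but cortisol and blood pressure only at the first two.

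**The concern.** Three things in the stated analysis do not serve the trial well.

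- **Precision.** With two time points, the group-by-time test of a mixed ANOVA is the same as a t-test on change scores. It fixes the slope on baseline at 1 instead of estimating it. In a trial this small, that gives up precision which data already collected could supply.
- **The third visit.** The six questionnaires are repeated at 4 weeks, but the model as described stops at postintervention. Whether an effect lasts is then not tested by any stated analysis.
- **Two models under one name.** A classical mixed ANOVA and a likelihood-based mixed model treat incomplete participants differently. An analyst who follows the label would not deliver the missing-data handling that the text promises.

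**Working it through.** **Inputs from the protocol (Sample Size).** "By assuming a study power of 0.8, 95% CI (α=0.05), and a moderate effect size of 0.25"; a repeated-measures ANOVA interaction with 2 groups; 36 required in total; 50 planned after allowing for drop-out. The number of measurements and the pre-post correlation are not given. The Results section reports 28 recruited.

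**Assumptions.** Two measurements, equal variances at both times, equal arms, two-sided 5% level, and r = 0.5 with 0.3 and 0.7 as the range.

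**Reproducing the 36.** The noncentrality is λ = f²·N·m/(1−r), with 1 and N−2 degrees of freedom at m = 2. With f = 0.25 and r = 0.5, λ = 0.0625 × 2 × N/0.5 = N/4. Power is 80.7% at N = 34 and 83.0% at N = 36, so the stated 36 is reproduced to within 2 participants; r of about 0.46 gives exactly 36. At r = 0.5, three measurements would give 28, so two fits better.

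**What f = 0.25 means here.** A difference D in mean change, in units of the score's SD, gives f = D/4 with two groups and two times. Hence D = 4 × 0.25 = 1.0 SD.

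**Variance.** Per participant and in units of σ²:
- change score: 2(1−r)
- baseline-adjusted: 1−r² = (1−r)(1+r)
- ratio: (1+r)/2, which is below 1 for every r below 1

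The ratio is 0.65, 0.75 and 0.85 at r = 0.3, 0.5 and 0.7, so the large-sample reduction is 35%, 25% and 15%. Over r from 0 to 0.9 it runs from 50% to 5%.

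**Cost of estimating the slope.** Multiply the adjusted variance by 1 + 1/(N−4). At r = 0.5 and N = 28: 0.75 × (1 + 1/24) = 0.781, a reduction of 21.9%. A simulation of 20,000 trials at N = 36 and r = 0.5 gave 23.2%, against 22.7% from the formula.

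**Power for 1.0 SD** (noncentral t, N−2 and N−3 degrees of freedom). N = 25 is half of the planned 50, 28 is the number recruited so far, and 36 is the stated requirement.

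| r | N | Variance reduction | Power, change score | Power, baseline-adjusted |
|---|---|---|---|---|
| 0.3 | 25 | 31.9% | 53% | 69% |
| 0.3 | 28 | 32.3% | 58% | 74% |
| 0.3 | 36 | 33.0% | 69% | 85% |
| 0.5 | 25 | 21.4% | 67% | 77% |
| 0.5 | 28 | 21.9% | 72% | 82% |
| 0.5 | 36 | 22.7% | 83% | 91% |
| 0.7 | 25 | 11.0% | 87% | 90% |
| 0.7 | 28 | 11.5% | 91% | 94% |
| 0.7 | 36 | 12.3% | 96% | 98% |

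At r = 0.5 the N for 80% power falls from 34 to 28.

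**Can the described random effects be fitted?** Two scores per participant have three distinct variances and covariances. A random intercept, a random slope, their covariance and a residual variance make four parameters. With two time points they cannot all be estimated.

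**The case against.** The change-score comparison is unbiased under randomisation, so the choice of model is a matter of efficiency and not an error. A protocol article may also leave covariates and covariance structure to a fuller plan. Both points stand, and they limit the weight of the precision argument. They do not answer the two inconsistencies, which lie in what the article itself states. The phrase about testing repeated measures over time might be stretched to cover the third visit, but the same section sets the comparison as pre versus post with two time points.

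Several stronger readings are tempting and do not hold:

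- **That the plan drops incomplete cases, perhaps 25 of 50.** Deletion follows from the label mixed ANOVA, not from the stated handling, which is maximum likelihood, all randomised participants and possible multiple imputation. The 50% is a planning allowance. The section defines drop-out as withdrawal from the intervention, which is not the same as a missing outcome. The Results section reports 2 withdrawals among 28.
- **That the correlation with baseline is ignored.** It enters the error term of the interaction through 1−r. Only the slope is fixed.
- **That within-group change will be taken as proof of effect.** Naming between and within comparisons is usual for a mixed ANOVA, and the section tests differential effects by interactions.
- **That clustering by therapy group is mishandled.** The fidelity section says that "progress of group sessions will be collected from mental health professionals after each session", but the delivery section describes administration to each participant, and no group number or size is given.

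The remedy has limits too. Participants with no post-baseline score leave a model whose outcomes are the two later visits. Preliminary analysis is already under way, so a change of model is more than an edit of wording.

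**Conclusion.** The point holds in limited form. The stated test is valid but less precise than one adjusted for baseline, for any correlation below 1. The size of the gain depends on a correlation that the protocol does not give, so no single percentage should be quoted without its assumption. The power figures also rest on reading f = 0.25 with two measurements. The gain is worth having with 28 recruited against a target of 50, and it is small if r is high.

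Two statements need to be reconciled whatever the correlation: the two-time-point analysis with the three-visit schedule for the questionnaires, and the mixed ANOVA label with the random effects and maximum likelihood attached to it. The change should be made before the final analysis.

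**What to change.** For the questionnaires, name one likelihood-based repeated-measures model (SPSS MIXED):

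- outcomes: scores at postintervention (t2) and at 4 weeks (t3)
- fixed effects: arm, visit, arm-by-visit, baseline score, baseline-by-visit
- unstructured covariance between the two visits, in place of random slopes and intercepts
- primary contrast: arm at t2; secondary contrast: arm at t3

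For cortisol and blood pressure, which have no 4-week measurement, use ANCOVA of the t2 value on baseline. Remove the mixed ANOVA wording, so that the text describes a single model. State that likelihood estimation is primary, and keep multiple imputation as a sensitivity analysis that includes participants with no post-baseline score.

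Record the change as a dated amendment through the route in the Protocol Amendments section, before any further comparison between arms, and say that preliminary analysis had already begun. The cost is revised analysis text, some programming and that disclosure. No new data are needed.
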